## 2. Materials and Methods

This is a pilot study using a repeated single-case experimental design (multiple baseline design) to explore the feasibility and clinical usefulness of a transdiagnostic emotion-based online group intervention (UP) for BS candidates with EDs or subclinical anxious or depressive symptoms attended to in a public mental health service. We have chosen this design for three reasons: (1) the unit of intervention and unit of data analysis is an individual case, specifically a cluster of participants; (2) the case provides its own control for comparison purposes because a number of variables are measured before the intervention and compared with measures during and after the intervention and (3) the variable is repeatedly measured within and across different conditions or levels of the independent variable. Furthermore, and because our main objective is to answer the question “Is the Unified Protocol able to improve the emotional state of people waiting for BS?”, we chose a multiple baseline design to improve experimental control throughout replication, introducing the independent variable at different points in time. The fundamental idea of choosing this type of design is that each of the participants can be their own control group [34].

The multiple baseline design involves the application of the treatment variable in a staggered way over time, through different observational units. This design is suitable for health services research interventions that are focused on changing patient behavior. This methodology facilitates a systematic comparison of pre-intervention and post-intervention measures [35], and conducting a preliminary assessment of a novel intervention [36]. Like randomized controlled trials (RCTs), the multiple baseline design can demonstrate that a significant change in behaviour has occurred and that is result of the intervention. One of the main limitations is that each participant must show changes only when the intervention is applied, and this issue, at a practical level is complicated, can make it difficult for the researcher to draw clear conclusions about the impact of the intervention. In order to reduce this limitation and improve the internal validity, researchers start treatment at different times across settings, behaviors, or people [37]. The multiple baseline design has advantages over the RCTs because this design requires fewer population groups and communities and they may act as their own controls [35]. In this sense, researchers often use this design with several people at once addressing the issue of external validity [37].

In the present investigation, all consecutive patients who are selected to undergo BS and who present anxiety or depressive symptoms or at least one diagnosis of ED, will be asked to participate. Once inclusion criteria are met (see “Inclusion and exclusion criteria” section), each patient will be randomly assigned to one of the multiple baseline conditions: 8, 12, or 15 evaluation days before the intervention. These multiple baseline conditions have been chosen following the current guides for single-case designs [34,38].

A random assignment will be carried out to reduce the threat of selection, and the fact of choosing three conditions is one of the established standards for this type of designs in order to reduce the threat of ambiguous temporal precedence and maturation [38]. Furthermore, the fact that all three conditions involve evaluation periods of 8, 12 and 15 days is due to the established standard of having a minimum of five data points in each phase to reduce the threat of attrition [38]. By choosing at least eight, we make sure to meet it even considering the probability that participants will forget to fill out the assessment one day. Actually, the reason for choosing those days is the temporal stability of the variables that we measured through the study.

In addition, the intervention will begin in a staggered manner with individual sessions (to reduce the threat of the history) and to reduce the threat of testing, a pre-treatment assessment will be performed prior to starting the baseline, to consider that the assessment process itself can have therapeutic effects on participants [38].

The study includes five assessment moments (pre-treatment, baseline, treatment, post-treatment, and follow-up, one every three months until two years after treatment completion). The flow chart of the study design is shown in Figure 1.

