The baseline and psychological intervention will be conducted between the period of acceptance for BS and the BS implementation, that last approximately one year in public health settings. The intervention will be carried out in an online group format through the Cisco Webex platform. The UP will be applied in twelve weekly 2-h online group sessions. To comply with the experimental design of the multiple baseline, when each participant completes the baseline evaluation, they will receive the first online session in individual format (to receive the first session in stages), then they will continue with the second session and the rest of the treatment in group format. The content of each session is shown in Table 2. Participants will receive the therapy support manual [11]. The online group will consist of five to eight participants, one therapist ([name]), and one co-therapist ([name]). For ethical reasons, if any of the patients feel uncomfortable during the study with the online group format, they may leave the group and receive individual onsite attention (treatment as usual). In this case, the content and estimated number of sessions will be the same, although the frequency will be stipulated by the mental health unit depending on its possibilities.

The study plans to conduct a follow-up assessment every three months until two years after treatment completion. All follow-ups will be conducted online. Considering the time interval of the baseline, the psychological intervention and the BS procedure, the two first follow-ups (three and six months after intervention) will be conducted before BS, and the rest will be conducted after BS. In addition, at the baseline and during treatment, the participants must fill out an online survey made up of 14 questions that will ask about the intensity of the emotions of happiness, sadness, anxiety, other emotions, difficulties in emotion regulation, body image, and emotional eating. Through this weekly evaluation, we expect to observe how the participants evolve in the different variables throughout the different treatment modules.

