#### 2.5.4. Assessment during Treatment

The assessment during treatment battery involves continuing to fill in the same baseline questions once a week. In addition, before starting each online session, participants will be asked to fill in an emotional scale to assess its presence, intensity, and interference during the last week. Participants can choose the emotion or emotions that should be assessed. The UP offers four different emotional rating scales: The Overall Anxiety and Depression Severity and Impairment Scales (OASIS; ODSIS [74,75,76]), Other Emotions Severity and Impairment Scale (e.g., guilt, shame, or anger) (OESIS [77]), and a Positive Emotion Severity and Impairment Scale (e.g., happiness) (PESIS [77]; Supplementary Materials). All of them are used in the UP to help patients to continuously monitor the scores throughout the sessions and their progress over the treatment.

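### A stagger of at most 7 days cannot separate a 12-week treatment effect from slow spontaneous improvement, so the maturation claim should be limited to abrupt or short-term change

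*Protocol article*

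**What the plan says.** Section 2 (Materials and Methods) randomises each participant to "8, 12, or 15 evaluation days before the intervention". It presents the use of three conditions as a published standard for such designs, adopted "in order to reduce the threat of ambiguous temporal precedence and maturation". Of multiple baseline designs in general, it says that, like randomised trials, they "can demonstrate that a significant change in behaviour has occurred and that is result of the intervention".

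Two reasons are given for the lengths. One is the "established standard of having a minimum of five data points in each phase to reduce the threat of attrition". The other is that "the reason for choosing those days is the temporal stability of the variables that we measured through the study", with no figure attached. Neither refers to the period over which change is expected.

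Section 2.2 states: "The UP will be applied in twelve weekly 2-h online group sessions". Only the first session is individual and timed by the end of each person's baseline; the group takes over from session 2. Under section 2.5.4, assessment during treatment means "continuing to fill in the same baseline questions once a week", after daily completion in the baseline.

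Table 3 marks the MINI, BDI-II and BAI at pre-treatment, post-treatment and follow-up, with no mark under baseline or treatment. BMI, the remaining primary outcome, is marked in every phase.

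**The concern.** Staggered starts guard against maturation in two ways. People who start later should improve later, by a visible amount. And the baseline should be long enough to show whether improvement was already under way. Both depend on how the stagger and the baseline compare with the time over which change unfolds.

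Here that time is about three months. The programme has twelve weekly modules, the article plans to track change module by module, and its first hypothesis compares pre-treatment, baseline and post-treatment scores. Participants enter with at least moderate symptom scores or a diagnosis, and such scores may drift down over three months without treatment. If improvement is gradual from either cause, the three conditions follow almost the same curve.

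What is at stake is the conclusion on clinical usefulness. Section 2 presents each participant as their own control. Without a stated limit, a pre-to-post fall in BDI-II or BAI could be read as caused by the Unified Protocol (UP) on evidence that this stagger cannot supply.

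**Working it through.** **The plan's own figures.** 3 × 20 = 60 participants, as section 2.1 states. With its 35% loss, 20 × 0.65 = 13 per condition, 39 in all, which agrees with the expectation in section 2.6 of fewer than 50. The article gives no figure for the adequacy of the stagger, so there is none to reproduce.

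**Inputs from the article.** Baselines of 8, 12 and 15 days; twelve weekly sessions; weekly measurement during treatment; 20 per condition; medium to large effects (section 2.1, no number).

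**Assumptions.** Effect D = 0.5 to 0.8 SD; linear build-up over 84 days; two-sided 5% test; normal approximation.

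**1. Time scales.**
- Largest stagger: 15 − 8 = 7 days. Steps: 12 − 8 = 4 and 15 − 12 = 3 days.
- Share of treatment: 7/84 = 8.3%. Counting only from first to last session (11 × 7 = 77 days), 7/77 = 9.1%.
- During treatment the items are completed every 7 days, so the whole stagger is one interval and each step is shorter than one.

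**2. Contrast between the 8- and 15-day conditions on a common day since entry, gradual effect.** Contrast = D × 7/84.
- D = 0.5: 0.042 SD. D = 0.8: 0.067 SD.
- Standard error with 20 per condition: √(2/20) = 0.316 SD for raw scores; √(2 × 2 × 0.3/20) = 0.245 SD for change scores, assuming a correlation of 0.7.
- Two-sided power runs from 5.2% (D = 0.5, raw: 3.38% + 1.82% in the two tails) to 5.9% (D = 0.8, change), barely above the 5% false-positive rate.
- With 13 per condition and raw scores it is 5.1% to 5.3%.

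**3. Outcomes measured only before and after (MINI, BDI-II, BAI), treated as a continuous score.** Under pure linear maturation, change is proportional to 84 + baseline days, which is 92, 96 and 99 days. Scaled to average D:

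| | 8 days | 12 days | 15 days | Spread |
|---|---|---|---|---|
| Maturation only, D = 0.5 | 0.481 | 0.502 | 0.517 | 0.037 |
| UP effect only, D = 0.5 | 0.500 | 0.500 | 0.500 | 0 |
| Maturation only, D = 0.8 | 0.769 | 0.803 | 0.828 | 0.059 |
| UP effect only, D = 0.8 | 0.800 | 0.800 | 0.800 | 0 |

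The two explanations differ by a spread of about 0.04 to 0.06 SD between conditions, against a standard error of 0.245 to 0.316 SD.

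**4. The opposite case: an abrupt effect at session 1.** On a day when the 8-day condition has started and the 15-day condition has not, the contrast is the full D. Power for D = 0.8 is about 72% with 20 per condition and 53% with 13. For D = 0.5 it is 35% and 25%. Here the stagger does carry information.

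**The case against.** The strongest reply is that the article claims little. It says that maturation is made less of a threat, not that it is removed, and it ties this to a cited standard on the number of conditions. The sentence likening the design to randomised trials describes a class of designs, and the next one admits that clear conclusions about impact can be hard to reach. The Discussion asks for caution because this is a pilot and calls for later randomised trials. All of this is fair. A reader might infer that the design offers no protection against maturation. The article does not support that: step 4 shows that an abrupt effect can be told apart, and fast spontaneous change would show in the daily items.

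What remains is narrower. For slow change the reduction is close to nil, and the claim is made without that limit. Section 2 names the difficulty of attributing change but offers staggered starts as the remedy. The Discussion's caution mentions neither maturation nor the length of the stagger.

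A second reply is that nobody plans to compare the 8- and 15-day conditions on a common day, and that the linear course is assumed. Both are true. The contrast is used here to measure how much information the stagger holds, not to criticise a planned test. Denser measurement or another test would leave the 0.04 to 0.07 SD unchanged.

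Two further inferences should be resisted.
- **That the baselines leave open a trend larger than the whole effect.** Pooling 60 complete daily series with independent days, the slope information is 20 × (42 + 143 + 280) = 9,300, and the 95% half-width projected to 84 days is 1.96 × 84/√9,300 = 1.71. That figure is in within-person daily SD of single items; 0.5 to 0.8 is in effect-size SD. The comparison would need the daily SD to exceed 0.5/1.71 = 0.29 to 0.8/1.71 = 0.47 of the effect-size SD, and the article gives no such ratio.
- **That the baselines must be lengthened.** On the assumptions of step 2 with raw scores, power is only 8 to 13% at a 28-day stagger and 12 to 24% at 42 days. Section 2.2 also places baseline, treatment and two follow-ups in a wait for surgery of about one year. Longer baselines are a trade-off, not a correction.

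**Conclusion.** The point holds for slow maturation only. A largest stagger of 7 days, about 8% of a 12-week programme, does not let the three conditions separate gradual UP benefit from gradual spontaneous improvement. It holds most clearly for the MINI, BDI-II and BAI, which have no measurement in the baseline phase. The protection against abrupt or fast change around session 1, on the daily items, stands.

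The time scales come straight from the article. The 0.04 to 0.07 SD contrast and the 5 to 6% power rest on the assumed D, the linear course, the two-sided 5% level and, for the upper power value, the correlation of 0.7. The article gives no time course for the effect; that it unfolds over weeks is inferred from the twelve-session programme, the module-by-module tracking and the pre-to-post hypothesis. The pilot can proceed, but the maturation claim should not stand without this limit.

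**What to change.** 1. In section 2 (Materials and Methods), limit the maturation claim. For example: the three randomised baseline lengths help to distinguish the intervention from abrupt or short-term change around the start of treatment on the daily items.
2. Add there that pre-to-post change over about 12 weeks, especially on the MINI, BDI-II and BAI, cannot be separated from slow spontaneous improvement, and qualify the sentence on attributing change to the intervention accordingly.
3. Carry the same limit into the Discussion, the Conclusions and the report of results wherever clinical usefulness is concluded.

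This costs a few sentences and a more modest causal claim. It needs no change to baseline lengths, visits or sample size. The pooled baseline slope of the daily items with its interval may be reported as an optional, descriptive addition; projected over 12 weeks it would be too imprecise to settle the question.

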### 2.1. Sample and Recruitment

The study recruitment will start in September 2020 until December 2024. The study will be conducted in a public mental health center in Spain (Mental Health Unit of the Regional Hospital of Vinaròs, Castellón). Participants will be people over 18 years of age who have anxious or depressive symptoms, or at least one diagnosis of EDs according to Diagnostic and Statistical Manual of Mental Disorders five edition criteria [39] and who have been selected for a subsequent BS.

To calculate the sample size, we drew on a study that proposed stepwise rules of thumb for pilot studies based on the target effect size and the size of the future trial [40]. Previous works that study the efficacy of CBT procedures either in person or online have shown large variations in effect sizes, obtaining mainly medium to large effect sizes [41,42]. Taking these data into account, and expecting a 90% powered main trial and assuming a sample loss of 35% [43] we established a sample size of 20 participants per experimental condition for the present study, that is, a total sample of 60 participants.

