### 2.6. Data Analysis

The analyses will be carried out with the statistical package IBM SPSS Statistics version 22.0 for Windows [78]. First, the sociodemographic characteristics of the sample will be analyzed with descriptive statistics, calculating the mean and standard deviation of the scores in the different questionnaires administered. Next, a missing-value analysis and the Little Missing Completely At Random (MCAR) test will be performed to determine whether or not the distribution of missing values is random, and therefore whether the last observation made (LOCF) can be used. Internal consistency will be explored using Cronbach’s alpha.

As the sample size is expected to be less than 50, the normal distribution of the variables will be verified with the Shapiro–Wilk normality test. Depending on the result of this test, parametric or non-parametric repeated measures analysis will be carried out to verify whether or not the differences in the scores of the variables measured at different times are statistically significant. In case the variables follow a normal distribution, parametric repeated measures analysis will be carried out, specifically the Multivariate Analysis of Variance (ANOVA), and in case the variables do not follow a normal distribution, non-parametric repeated measures analysis will be carried out, specifically the Friedman test. If the repeated measures analysis show statistically significant differences between the evaluation time points, post-hoc comparisons will be carried out to correct the level of significance to avoid increasing the type I error. Thus, regarding adjustment for multiple comparisons, the Bonferroni correction will be carried out in case of having performed parametric analysis, and the Wilcoxon signed rank test in case of having performed non-parametric analysis in the comparison of means. More detailed information on this has been added in the data analysis section, explaining step by step which statistical analyzes will be carried out.

Finally, the Reliable Change Index (RCI), which assesses the clinically significant change obtained to determine in which variables the scores have approached those of the normative sample, will be calculated. A clinically significant change will be considered if the RCI score obtained is equal to or greater than 1.96 [79].

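### The sample size of 20 per baseline condition is not linked to the pooled within-person tests that the study plans and expects to be significant

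*Protocol article*

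**What the plan says.** Section 2.1 (Sample and Recruitment) takes the size from "stepwise rules of thumb for pilot studies based on the target effect size and the size of the future trial". It refers to earlier CBT studies with mostly medium to large effects, without a number, scale or outcome, and concludes: "expecting a 90% powered main trial and assuming a sample loss of 35% [43] we established a sample size of 20 participants per experimental condition". Three conditions of 20 give 60.

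Section 2 (Materials and Methods) defines the conditions: "each patient will be randomly assigned to one of the multiple baseline conditions: 8, 12, or 15 evaluation days before the intervention". Section 2.2 gives everyone the same twelve-session intervention. Section 2 also says that each participant serves as their own control.

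Section 2.6 (Data Analysis) plans a repeated-measures ANOVA or a Friedman test "to verify whether or not the differences in the scores of the variables measured at different times are statistically significant". If the overall test is significant, post-hoc comparisons follow, and "the Bonferroni correction will be carried out in case of having performed parametric analysis". The number of comparisons is not fixed. The section also expects an analysed sample below 50, and adds the Reliable Change Index (RCI) and a visual analysis of slopes. None of these compares the three baseline lengths.

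Table 4 lists, among the group results, significant differences between time points in the desired direction.

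**The concern.** The unit in which the study is sized (a baseline condition) is not the unit in which it is analysed at group level (the pooled cohort over time). The only power figure in the article concerns another trial. Yet the group tests are to be read as evidence of clinical usefulness, and nothing says what size of change they can detect.

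Section 2.6 makes this worse in one respect. The pre-post comparison, which bears most directly on the study question, is not singled out. It is reached only after a significant overall test, as one of an unspecified number of Bonferroni-corrected pairs. The more follow-ups enter that family, the less power it has. A real medium improvement on BDI-II or BAI could then be reported as not significant, and a reader could not tell a weak test from an absent effect.

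**Working it through.** **The plan's own figure.** 3 x 20 = 60 is consistent. The 20 itself cannot be derived, because the rule's base number and the effect category used are not given. Working back through the 35% loss, 20 x 0.65 = 13 per condition, or 13 x 3 = 39 in total. This agrees with the expectation in section 2.6 of fewer than 50.

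**Inputs from the article**
- 60 recruited and 35% loss (section 2.1), so n = 39 if all the loss occurs before post-treatment.
- Questionnaire occasions (sections 2 and 2.5, Table 3): pre-treatment, post-treatment and eight quarterly follow-ups over two years, so 10.
- All pairs of 10 occasions: 10 x 9 / 2 = 45. This is an upper bound; section 2.6 does not say that all will be tested.

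**Assumptions not in the article**
- Two-sided 5% for each outcome.
- Medium effect d = 0.5 and large effect d = 0.8, in units of the raw standard deviation.
- Pre-post correlation r = 0.5, range 0.3 to 0.7.

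**Formulas.** The standardised within-person change is dz = d / sqrt(2(1 - r)). For d = 0.5 this is 0.423, 0.500 and 0.645 at r = 0.3, 0.5 and 0.7. Power comes from the noncentral t distribution with n - 1 = 38 degrees of freedom and noncentrality dz x sqrt(n). At r = 0.5 the noncentrality is 0.5 x sqrt(39) = 3.12. The level is 0.05 divided by the number of contrasts.

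**Power at n = 39, d = 0.5**

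| Contrasts corrected for | Level | Critical t | r = 0.3 | r = 0.5 | r = 0.7 |
|---|---|---|---|---|---|
| 1 | 0.05 | 2.02 | 73% | 86% | 98% |
| 2 | 0.025 | 2.33 | 62% | 78% | 95% |
| 3 | 0.0167 | 2.51 | 56% | 73% | 93% |
| 45 | 0.0011 | 3.53 | 21% | 36% | 69% |

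**Other cases**
- d = 0.8, n = 39, 45 pairs: 92% at r = 0.5 (75% at 0.3, 99.7% at 0.7).
- d = 0.5, r = 0.5, all 60 analysed: 97% for one contrast, 92% for three pairs, 67% for 45.
- Overall repeated-measures test, n = 39, sustained shift of 0.5 SD, r = 0.5: 90% with three occasions, 84% with ten.

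**Change dz detectable with 90% power at n = 39:** 0.53 for one contrast at 0.05, 0.58 at 0.025, 0.61 for three pairs and 0.78 for 45. The level matters when the figure is quoted: at alpha 0.025, a change of 0.533 has only 83.5% power.

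**The case against.** The strongest reply is that this is a pilot, called so throughout, with feasibility among its aims. A pilot need not be powered for efficacy, and section 4 already asks for cautious interpretation and further randomised trials. The individual case is the stated unit of analysis. Hypothesis 1 and the individual results in Table 4 rest on the RCI, and section 2.6 adds visual analysis. None of these depends on the power of a paired test. The three baseline lengths serve replication and internal validity, not an efficacy comparison. The contrast family may be defined in an analysis plan that is not shown.

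Much of this stands. It does not remove the mismatch, because Table 4 does list significant group tests as an expected result and section 2.1 gives a reason for its number that does not bear on those tests.

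Three stronger readings are tempting and should be resisted:
- A reader might infer that the study misses a 90% power it promised. It promises none; the 90% is attached to the later trial.
- A reader might infer that the planned tests fall well short of 90% for medium effects in general. One pre-post contrast has 86%, and 92.5% at a correlation of 0.6. The large shortfall needs correction over several occasions or a weaker correlation. The 45-pair case is only what the text allows, and Bonferroni is named only for the parametric branch.
- A reader might infer that the cited rule was misapplied because it presumes arms to be compared. The article does not describe the rule closely enough to say so.

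**Conclusion.** The point holds in a limited form. The number per baseline condition comes from a rule for a later trial and has no stated connection to the pooled within-person tests. At d = 0.5, power for the pre-post comparison lies anywhere from 86% to 36%, depending only on how many pairs share the correction, and the article leaves that open. Large effects are detectable with about 92% power at r = 0.5 even in the worst case.

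These figures rest on the assumed 5% level, effect size and correlation, and on all the loss falling before post-treatment. If some of it falls later, during the two years of follow-up, power at post-treatment is higher.

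The sample size does not need to change, and rewording section 2.1 alone would alter no result. The useful gain is in section 2.6: making pre versus post a planned contrast on two scales gives 78% power, against 36% when it is one of 45 corrected pairs, with the same patients.

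**What to change.** Keep N = 60.

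1. **Section 2.6.** Name pre-treatment versus post-treatment on BDI-II and BAI as the planned group contrasts, tested directly at alpha 0.025 each and not conditional on an overall test. Make the pairwise comparisons with follow-ups secondary, with their own correction. Say how the other primary outcomes, MINI diagnosis and BMI, are handled.
2. **Section 2.1.** State that the 90% refers to a later trial and that the baseline conditions are not compared for efficacy. Add that about 39 completers give 90% power for a standardised within-person change of 0.58 at alpha 0.025. The figure of 0.53 applies only to a single uncorrected contrast and should not be quoted for two corrected scales.

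The cost is rewording, with no added patients or visits. The downside is that follow-up pairwise comparisons become secondary.
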